### **13.2.10 Preparation of HIV gag DNA Plasmid 1500 mcg / IL-12 DNA 500 mcg or Placebo (Group 3)**

#### *HIV gag DNA Plasmid 1500 mcg / IL-12 DNA 500 mcg*

All vials should be visually inspected prior to use. If any vial contains material different from its description above, do not use the vial and contact the protocol pharmacist. Using aseptic technique, the pharmacist will use a 1 mL syringe to withdraw 0.4 mL from the vial of IL-12 DNA 2mg/mL vial (Lot # 76172001A). The contents of this syringe will then be slowly injected into the vial containing 1.2 mL of HIV gag DNA Plasmid (2 mg/mL). The pharmacist should avoid creating bubbles. To prevent aerosolization, the pharmacist should, before removing the needle from the vial, bring the needle above the level of the liquid and allow excess air to rise into the syringe. Remove the syringe from the vial and discard into a sharp's container. The pharmacist will mix the solution in the vial by gentle swirling (avoid creating bubbles). The final product should be a clear colorless liquid containing 1.6 mL of a 3:1 mixture of HIV gag DNA Plasmid: IL-12 DNA, consisting of 1500 mcg/mL of HIV gag DNA and 500 mcg/mL of IL-12 DNA. Using a new 3 mL syringe, the pharmacist will withdraw 1 mL of this final product. The pharmacist will label the syringe as HIV gag DNA Plasmid 1500 mcg / IL-12 DNA 500 mcg or placebo. The final product must be administered within 4 hours after preparation. It must be stored at 2 to 8°C if not administered immediately after preparation.

*Any unused portion of entered vials and expired pre-filled syringes should be disposed of in accordance with institutional or pharmacy policy.*

#### *Placebo (for HIV gag DNA Plasmid 1500 mcg / IL-12 DNA 500 mcg)*

Using aseptic technique, the pharmacist will withdraw 1 mL of sodium chloride injection USP, 0.9% into a 3 mL syringe. The pharmacist will label the syringe as HIV gag DNA Plasmid 1500 mcg / IL-12 DNA 500 mcg or placebo. The final product must be administered within 4 hours after preparation. It must be stored at 2 to 8°C if not administered immediately after preparation.

*Any unused portion of entered vials and expired pre-filled syringes should be disposed of in accordance with institutional or pharmacy policy.*

### **13.2.11 Preparation of HIV gag DNA Plasmid 1500 mcg / IL-12 DNA 1500 mcg or Placebo (Group 4)**

#### *HIV gag DNA Plasmid 1500 mcg / IL-12 DNA 1500 mcg*

All vials should be visually inspected prior to use. If any vial contains material different from its description above, do not use the vial and contact the protocol pharmacist. Using aseptic technique, the pharmacist will use a 3 mL syringe to withdraw 0.9 mL of HIV gag DNA Plasmid 2 mg/mL vial. The contents of this syringe will then be slowly injected into the vial containing 0.9 mL of IL-12 DNA (2 mg/mL) (Lot # 76172001A). The pharmacist should avoid creating bubbles. To prevent aerosolization, the pharmacist should, before removing the needle from the vial, bring the needle above the level of the liquid and allow excess air to rise into the syringe. Remove the syringe from the vial and discard into a sharp's container. The pharmacist will mix the solution in the vial by gentle swirling (avoid creating bubbles).

The final product should be a clear colorless liquid containing 1.8 mL of a 1:1 mixture of HIV *gag* DNA Plasmid: *IL-12* DNA, consisting of 1000 mcg/mL of HIV *gag* DNA and 1000 mcg/mL of *IL-12* DNA. Using a new 3 mL syringe, the pharmacist will withdraw 1.5 mL of this final product. The pharmacist will label the syringe as HIV *gag* DNA Plasmid 1500 mcg / *IL-12* DNA 1500 mcg or placebo. The final product must be administered within 4 hours after preparation. It must be stored at 2 to 8°C if not administered immediately after preparation.

*Any unused portion of entered vials and expired pre-filled syringes should be disposed of in accordance with institutional or pharmacy policy.*

*Placebo (for HIV gag DNA Plasmid 1500 mcg / IL-12 DNA 1500 mcg)*

Using aseptic technique, the pharmacist will withdraw 1.5 mL of sodium chloride injection USP, 0.9% into a 3 mL syringe. The pharmacist will label the syringe as HIV *gag* DNA Plasmid 1500 mcg / *IL-12* DNA 1500 mcg or placebo. The final product must be administered within 4 hours after preparation. It must be stored at 2 to 8°C if not administered immediately after preparation.

*Any unused portion of entered vials and expired pre-filled syringes should be disposed of in accordance with institutional or pharmacy policy.*

### **13.2.12 Preparation of HIV *gag* DNA Plasmid 1500 mcg / IL-12 DNA 1500 mcg or Placebo (Groups 6 and 7)**

*HIV gag DNA Plasmid 1500 mcg / IL-12 DNA 1500 mcg*

All vials should be visually inspected prior to use. If any vial contains material different from its description above, do not use the vial and contact the protocol pharmacist. Using aseptic technique, the pharmacist will use a 3 mL syringe to withdraw 0.9 mL of HIV *gag* DNA Plasmid 2 mg/mL vial. The contents of this syringe will then be slowly injected into the vial containing 0.9 mL of *IL-12* DNA (2 mg/mL) (Lot # 76180001A). The pharmacist should avoid creating bubbles. To prevent aerosolization, the pharmacist should, before removing the needle from the vial, bring the needle above the level of the liquid and allow excess air to rise into the syringe. Remove the syringe from the vial and discard into a sharp's container. The pharmacist will mix the solution in the vial by gentle swirling (avoid creating bubbles). The final product should be a clear colorless liquid containing 1.8 mL of a 1:1 mixture of HIV *gag* DNA Plasmid: *IL-12* DNA, consisting of 1000 mcg/mL of HIV *gag* DNA and 1000 mcg/mL of *IL-12* DNA. Using a new 3 mL syringe, the pharmacist will withdraw 1.5 mL of this final product. The pharmacist will label the syringe as HIV *gag* DNA Plasmid 1500 mcg / *IL-12* DNA 1500 mcg or placebo. The final product must be administered within 4 hours after preparation. It must be stored at 2 to 8°C if not administered immediately after preparation.

*Any unused portion of entered vials and expired pre-filled syringes should be disposed of in accordance with institutional or pharmacy policy.*

*Placebo (for HIV gag DNA Plasmid 1500 mcg / IL-12 DNA 1500 mcg)*

Using aseptic technique, the pharmacist will withdraw 1.5 mL of sodium chloride injection USP, 0.9% into a 3 mL syringe. The pharmacist will label the syringe as HIV *gag* DNA Plasmid 1500 mcg / *IL-12* DNA 1500 mcg or placebo. The final product must be administered within 4 hours after preparation. It must be stored at 2 to 8°C if not administered immediately after preparation.

*Any unused portion of entered vials and expired pre-filled syringes should be disposed of in accordance with institutional or pharmacy policy.*

### **13.2.13 Preparation of MEP 1000mcg / RC529-SE 50mcg / GM-CSF 250 mcg or Placebo (Group 7)**

*MEP 1000mcg / RC529-SE 50mcg / GM-CSF 250 mcg*

All vials should be visually inspected prior to use. If any vial contains material different from its description above, do not use the vial and contact the protocol pharmacist. Using aseptic technique (in a laminar flow hood), the pharmacist will use a 1 mL syringe to withdraw 0.6 mL of sodium succinate diluent from the vial. The contents of this syringe will then be injected into the HIV CTL Peptides vial (625 mcg/mL per peptide). The vial should be gently tapped to re-suspend the HIV CTL Peptides until no solid cake material is visible. Still using aseptic technique (in a laminar flow hood), the pharmacist will use a new 1 mL syringe to withdraw 0.15 mL of RC529-SE. The contents of this syringe will then be added to the re-suspended HIV CTL Peptides vial. Again, using a new 1 mL syringe, the pharmacist will aseptically withdraw 0.75 mL of GM-CSF injection (500 mcg/mL) from the vial and inject the contents of this syringe into the vial containing re-suspended HIV CTL Peptides/ RC529-SE. The vial should then be swirled gently to mix the contents.

Prior to injection, using a 3 mL syringe, the pharmacist will withdraw 1 mL of the HIV CTL Peptides/ RC529-SE/GM-CSF admixture. The final product (HIV CTL Peptides 1000 mcg total dose admixed with 50 mcg of RC529-SE and 250 mcg of GM-CSF) should be labeled as PEP/RC529-SE/GM-CSF or placebo. The pharmacist must apply a blue overlay to the syringe and the syringe must be labeled with a 3 hour expiration (based on time of preparation). The syringe should be stored at 2° to 8°C (36° to 46°F) if not for immediate injection.

*Any unused portion of entered vials and expired pre-filled syringes should be disposed of in accordance with institutional or pharmacy policy.*

*Placebo for MEP 1000mcg / RC529-SE 50mcg / GM-CSF 250 mcg*

All vials should be visually inspected prior to use. If any vial contains material different from its description above, do not use the vial and contact the protocol pharmacist. Using aseptic technique, the pharmacist should withdraw 1 mL of sodium chloride injection USP, 0.9% into a 3 mL syringe. The syringe should be labeled as MEP/RC529-SE/GM-CSF or placebo. The pharmacist must apply a blue overlay to the syringe and the syringe must be labeled with a 3 hour expiration date (based on time of preparation). The syringe should be stored at 2° to 8°C (36° to 46°F) if not for immediate injection (to prevent unblinding).

*Any unused portion of entered vials and expired pre-filled syringes should be disposed of in accordance with institutional or pharmacy policy.*

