## 7 Study type, study population, and eligibility criteria

The study is a Phase I multicenter, randomized, placebo-controlled, double-blind trial to evaluate the safety and immunogenicity of HIV-1 *gag* DNA vaccine alone and in combination with *IL-12* DNA adjuvant as a 3 dose priming series. Due to differences in injection volumes, study participants and study staff cannot be blinded to study group assignment. The study is double-blinded regarding vaccine study product versus placebo administration. Participants in Part B will also receive 2 booster vaccinations either with the above plasmids or with HIV CTL MEP vaccine or with placebo. Participants will be recruited and screened. Those determined to be eligible, based on the inclusion and exclusion criteria (see Table 7-1 and Table 7-2), will be enrolled in the study and followed for a total period of 9 months in Part A and 15 months in Part B.

Participants will receive priming series vaccinations at Days 0, 28, and 84 (Months 0, 1 and 3). Booster vaccinations for participants in Part B will be administered at Days 168 and 273 (Months 6 and 9). All vaccinations will be administered by intramuscular injection in the deltoid using needle/syringe in the outpatient setting.

Participants will be healthy HIV-1-uninfected (seronegative) adults who comprehend the purpose of the study and have provided written informed consent.

See Table 7-1 for inclusion criteria and Table 7-2 for exclusion criteria. Final eligibility determination will depend on results of laboratory tests, medical history, physical examinations, and answers to the self-administered and/or interview questions.

See Table 12-1 for screening procedures.

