### 9.4 Accrual and sample size

Recruitment will target 156 healthy, HIV-uninfected adult participants.

Part A will consist of 4 groups. Groups 1 and 2 will be enrolled simultaneously with participants randomized to receive either *gag* DNA or placebo (Group 1), or *gag* DNA plus *IL-12* DNA (100 mcg) or placebo (Group 2) in a (10:2) ratio within each group. Groups 3 and

4 will proceed sequentially according to dose escalation rules outlined in Sections 8.3 and 14.7.5. Groups 3 and 4 will each enroll participants randomized to receive either *gag* DNA plus *IL-12* DNA (maximum tolerated dose, MTD) or placebo in a (10:2) ratio.

Part B will consist of 3 groups (Groups 5, 6, 7) and will follow Part A according to rules outlined in Section 8.4. Groups 5, 6, and 7 will be enrolled simultaneously and randomized to receive either *gag* DNA (1500 mcg) for both prime and booster vaccinations or placebo (Group 5), or *gag* DNA plus *IL-12* DNA (MTD) for both prime and booster vaccinations or placebo (Group 6), or *gag* DNA plus *IL-12* DNA (MTD) for prime and HIV CTL MEP for booster vaccinations or placebo (Group 7), each group with a (30:6) ratio for vaccine to placebo.

Note that study design blinds participants and site staff to vaccine or placebo arms of each group, but participants will not be blinded as to which group they are in.

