**13.2.7 Placebo (Sodium Chloride Injection USP, 0.9%, NaCl 0.9%)**

Sodium chloride injection USP, 0.9% will be used as the placebo for all groups. The volume to be administered will vary from group to group to maintain the blind between active and placebo treatment (T and C) in each group. The vials must be stored as directed by the manufacturer of the product unless otherwise instructed.

**13.2.8 Preparation of HIV gag DNA Plasmid 1500 mcg or Placebo (Groups 1 and 5)***HIV gag DNA Plasmid 1500 mcg*

All vials should be visually inspected prior to use. If any vial contains material different from its description above, do not use the vial and contact the protocol pharmacist. Using aseptic technique, the pharmacist will use a 3 mL syringe to withdraw 0.75 mL of HIV gag DNA Plasmid from the vial. The pharmacist will label the syringe as HIV gag DNA Plasmid 1500mcg or Placebo. It should be stored at 2° to 8°C (36° to 46°F) if not for immediate injection. The syringe must be labeled with a 4 hour expiration date/time.

*Any unused portion of entered vials and expired pre-filled syringes should be disposed of in accordance with institutional or pharmacy policy.*

*Placebo (for HIV gag DNA Plasmid 1500 mcg)*

All vials should be visually inspected prior to use. If any vial contains material different from its description above, do not use the vial and contact the protocol pharmacist. Using aseptic technique, the pharmacist will use a 3 mL syringe to withdraw 0.75 mL of Sodium Chloride Injection USP, 0.9% from the vial. The pharmacist will label the syringe as HIV gag DNA Plasmid 1500mcg or Placebo. It should be stored at 2° to 8°C (36° to 46°F) if not for immediate injection. The syringe must be labeled with a 4 hour expiration date/time.

*Any unused portion of entered vials and expired pre-filled syringes should be disposed of in accordance with institutional or pharmacy policy.*

**13.2.9 Preparation of HIV gag DNA Plasmid 1500 mcg / IL-12 DNA 100 mcg or Placebo (Group 2)***HIV gag DNA Plasmid 1500 mcg / IL-12 DNA 100 mcg*

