### **13.2.14 Pharmacy procedures to preserve blinding**

The pharmacist will prepare the doses for administration and dispense to the clinic. To preserve blinding, a blue overlay will be placed on syringes containing MEP / RC529-SE / GM-CSF or its placebo.

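### Section 13.2.13 words the active and placebo CTL MEP syringe labels differently, so literal compliance could unblind the two Group 7 boosters

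*Protocol*

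**What the plan says.** Section 7 describes the masking of the trial: "The study is double-blinded regarding vaccine study product versus placebo administration". Group membership is open because injection volumes differ between groups. Section 9.4 says who is masked: "Note that study design blinds participants and site staff to vaccine or placebo arms of each group".

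Section 13.2.13 covers the booster product, which only Group 7 receives. It directs that the active preparation "should be labeled as PEP/RC529-SE/GM-CSF or placebo". For the saline preparation it directs: "The syringe should be labeled as MEP/RC529-SE/GM-CSF or placebo".

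Section 13.2.14 adds one measure for this product: "To preserve blinding, a blue overlay will be placed on syringes containing MEP / RC529-SE / GM-CSF or its placebo".

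The DNA products are handled differently. In Section 13.2.8, for example, the active and the placebo instructions contain the same sentence: "The pharmacist will label the syringe as HIV gag DNA Plasmid 1500mcg or Placebo".

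**The concern.** A label that names the product and ends with the words or placebo conceals the arm only if both syringes carry the same text. Here the text depends on the arm, so the label could carry the information that it is meant to withhold.

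Vaccine against placebo within a group is the only comparison the trial keeps blind. The primary objective of Part B is safety and tolerability. Much of the evidence is open to influence by knowledge of treatment:

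- Local and systemic reactions are assessed by site staff shortly after injection and then by staff or the participant through Day 3 (Table 14-1).
- The Part B pause criteria count vaccine-related events, including subjective symptoms (Table 14-3).
- Stopping an individual's vaccinations for a Grade 3 or 4 event depends on a judgement of relatedness (Section 14.5.2).

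Group 7 is the only group given CTL MEP, so no other group in this trial offers a blinded reading of that product.

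**Working it through.** There is no statistical figure to reproduce. The check is a comparison of texts, followed by a count of the injections affected.

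**Label text, active against placebo**

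| Section | Groups | Active and placebo label text |
|---|---|---|
| 13.2.8 | 1 and 5 | same |
| 13.2.9 | 2 | same |
| 13.2.10 | 3 | same |
| 13.2.11 | 4 | same |
| 13.2.12 | 6, and 7 (priming) | same |
| 13.2.13 | 7 (boosters) | differ: PEP for active, MEP for placebo |

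**Is PEP another name for the product?** Section 13.2.3 lists the product's names, and MEP is among them but PEP is not. The heading and both sub-headings of Section 13.2.13, its placebo label and Section 13.2.14 all use MEP. PEP stands alone in the active label instruction. This points to a typing slip and not to an intended code.

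**Does another provision override the two texts?** None does. Section 13.2.14 deals only with the overlay, and it does not give a common label or say that the overlay hides the label. The overlay has a separate purpose: RC529-SE is a milky emulsion (Section 13.2.4) and the placebo is saline, so the syringe contents would look different without it.

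**Largest possible extent**

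- Group 7 participants: 30 vaccine + 6 placebo = 36 (Section 9.4).
- CTL MEP or matching placebo boosters per participant: 2, at Months 6 and 9 (Section 7).
- Injections: 36 × 2 = 72, of which 30 × 2 = 60 are active and 6 × 2 = 12 are placebo.
- Planned Part B injections: 108 participants × 5 = 540, so the affected share is 72 / 540 = 13%.
- Share of the pooled Part B placebo recipients who are in Group 7: 6 / 18 = one third.

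The count of 72 assumes that every participant receives both boosters and that every site copies the text exactly.

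**The case against.** The intent of the protocol is plain. All other products have matching labels. Both CTL MEP syringes get an overlay, and the placebo text states that the syringe is kept cold to avoid unblinding. A pharmacist may well notice the slip and use one label. Neither text names the contents outright, so someone would have to notice the one-letter difference and connect it with the arm.

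Other safeguards also apply. Section 13.3 bars whoever gives a dose from being responsible for clinical follow-up of that dose, and it lets a pharmacist give the injection where the law allows. The daily and weekly safety reviews are blinded (Sections 14.7.1 and 14.7.2), and nothing suggests that those reviewers see syringes. The ELISpot and ICS assays are done at laboratories away from the clinic (Appendix C).

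Most of this stands and it limits the point. A reader might infer that the label by itself unblinds both boosters, or that reactogenicity and relatedness will be judged with treatment known. The documents do not support that reading. It needs literal copying, then decoding, and then the knowledge reaching an assessor or the participant. Nor does the label undo the overlay, which still masks the appearance of the contents.

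The objection does not remove the point. Section 13.2.13 is the dispensing instruction, and following it exactly is what is asked of pharmacists. The labelled syringe goes to the clinic, where the participant may see it and later report symptoms. Decoding is not hard, because the key is printed in the protocol. Where a site sees enough Group 7 participants, the 30:6 allocation would also suggest that the rarer label is placebo.

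**Conclusion.** The instruction is wrong as written: it gives arm-specific label text in a trial whose only blind is vaccine against placebo within group. The fault is an internal inconsistency, very probably a drafting slip, and not a deliberate design choice.

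The consequence is conditional. If pharmacists copy the text exactly, and if site staff or participants see and interpret the difference, treatment could become known at the two Group 7 boosters. The ceiling is 36 participants and 72 injections. The Group 7 priming doses, all of Part A, and Groups 5 and 6 are unaffected. The separation of injector and follow-up in Section 13.3 lowers the risk without removing it.

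The text should be corrected before the first Group 7 booster, because the change is trivial and lost blinding cannot be restored.

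**What to change.** In Section 13.2.13, use one identical label text for the active and the placebo syringe, with the MEP wording that the rest of the section already uses. Repeat that text in Section 13.2.14 so that the blinding procedure covers the label as well as the overlay. Send it to site pharmacists by clarification memo, a route that the Protocol history section provides for, before the first Group 7 booster at Month 6.

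The cost is a one-word correction and a short notice to pharmacies. Dose, schedule, sample size and analysis are unchanged.

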### **13.2.14 Pharmacy procedures to preserve blinding**

The pharmacist will prepare the doses for administration and dispense to the clinic. To preserve blinding, a blue overlay will be placed on syringes containing MEP / RC529-SE / GM-CSF or its placebo.

## **13.3 Study product administration**

All vaccinations are to be given intramuscularly into the deltoid muscle. The needle length should be appropriate for the participant's weight.

When preparing a dose in a syringe and administering the dose, consideration should be given to the volume of solution that may remain in the needle after the dose is administered. The pharmacy and clinic staffs are encouraged to work together to administer the dose specified in the protocol.

The person who administers the dose must not be the same individual who is responsible for clinical follow-up of that dose. At sites where registered pharmacists are legally authorized to administer drug, the HVTU may choose to have the HVTU pharmacist administer the vaccinations.

### 13.3.1 Administration of vaccinations

Syringes should be kept refrigerated at 2° to 8°C (36° to 46°F) until just prior to injection unless the administration is immediately after preparation. Administer the vaccine into the deltoid muscle after preparation of the site with alcohol. The same deltoid should be used at each vaccination visit unless medically contraindicated. If the injection is administered in the opposite deltoid due to a medical contraindication, the appropriate study staff should document this clearly and submit a Study Product Administration Error form. Under this circumstance, this is NOT a protocol violation.

**As significant adverse experiences—including cardiac arrest and death—have occurred with intravascular delivery of bupivacaine, it is essential that aspiration for blood be performed prior to injection of all *gag* DNA, *IL-12* DNA, or their placebo injections to ensure that i.v. delivery does not occur.**

